| **Administration dose** | 1. **Donafenib** : 200 mg, Bid, to be taken orally starting 3-7 days before the first HAIC treatment; 2. **Sintilimab**: 200 mg, Q3W, intravenous infusion 0-1 days before each HAIC treatment; 3. **HAIC:** FOLFOX regimen hepatic arterial infusion, Q3W, the total number of HAIC treatments will be determined by the investigator based on the patient's actual condition as needed (chemotherapy dose: Oxaliplatin 85 mg/m^2^ infusion over 2 hours, Leucovorin 400 mg/m^2^ infusion over 2 hours, 5-Fu 400 mg/m^2^ bolus over 10 minutes, followed by continuous infusion of 5-Fu 1200 mg/m^2^ over 23 hours);   **Note:**  This study sets a safety lead-in period, during which the first 6 subjects enrolled in the study will undergo gradual safety monitoring. Each patient will receive oral administration of donafenib [200 mg, Bid] in combination with intravenous infusion of sintilimab injection [200 mg, Q3W], along with HAIC treatment. The monitoring window is from the first administration of donafenib treatment to 21±3 days after the first HAIC treatment (i.e., from D1 of the donafenib monotherapy period to C2D1 of the combination therapy period). If ≥2 cases of dose-limiting toxicity (DLT) are observed among the first 6 subjects, and the research team assesses that the toxicity is solely related to donafenib treatment, the initial dose for subsequent enrolled patients receiving donafenib treatment will be adjusted to 100 mg Bid.  During the safety induction period, if a subject does not complete the tolerance observation period (approximately 21±3 days after the first HAIC treatment) due to non-dose tolerance reasons, they will be replaced by a new subject.  After the safety induction period, any enrolled subjects who withdraw from the trial early are not allowed to have additional subjects enrolled as replacements. Furthermore, the corresponding number of the withdrawn subject is not allowed to be reused by other new subjects. |

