| **Dose adjustment scheme** | 1) Donafenib dose adjustment scheme: If grade 4 hematologic toxicity or grade 3 non-hematologic toxicity occurs, temporarily discontinue the drug (according to NCI CTCAE V5.0 standards). After the first suspension of medication, if the adverse reactions recover to ≤ Grade 1 within 1 week, continue taking the original dose; If recovery to ≤ Grade 1 occurs within 2 weeks of suspension, then reduce the dose to 200 mg qd; If the dose is adjusted and medication is suspended again, if recovery to ≤ Grade 1 occurs within 2 weeks, then reduce the dose to 200 mg qod, with a maximum of 2 dose adjustments allowed. If recovery to normal or CTCAE Grade 1 cannot be achieved within 2 weeks after stopping the medication, then permanently discontinue the medication. If Grade 4 hematologic toxicity or Grade 3 non-hematologic toxicity occurs again (the 3rd occurrence), then permanently discontinue the medication.  At an initial dose of 200 mg bid, the dose adjustment scheme is as follows:   \| Initial dose \| First dose reduction \| Second dose reduction \| \| --- \| --- \| --- \| \| 200mg bid \| 200mg qd \| 200mg qod \|   If the initial dose of donafenib is adjusted to 100 mg bid due to the observation of ≥2 cases of DLT in the first 6 patients, the dose adjustment principles will be consistent with those at 200 mg bid, and the specific dose adjustment scheme is as follows:   \| Initial dose \| First dose reduction \| Second dose reduction \| \| --- \| --- \| --- \| \| 100mg bid \| 100mg qd \| 100mg qod \|  1. **Sintilimab dose adjustment scheme**: Dose adjustment of sintilimab is not permitted throughout the study; when intolerable toxicity related to sintilimab occurs, the investigator may decide to suspend or permanently discontinue sintilimab administration.   If a subject experiences a grade 2 drug-related irAE or a grade 3 or higher other AE (refer to the ESMO guidelines for the management of toxicity related to immune checkpoint inhibitors), the subject must suspend the administration of Sintilimab, with a maximum delay of 7 days; the subsequent administration schedule will be adjusted accordingly. If the administration is delayed for more than 7 days, it will be considered a missed dose, and the subject will receive the next cycle of administration according to the original schedule (calculated from the date of the first administration of Sintilimab). If treatment-related adverse reactions have not recovered to grade 0-1 or baseline levels within 6 weeks after the last dose of Sintilimab injection, the administration of Sintilimab injection should be permanently discontinued. Additionally, if the subject discontinues the medication for more than 6 weeks and the investigator determines that the risks of continuing treatment outweigh the benefits, the subject must permanently discontinue Sintilimab.  3) HAIC: In the HAIC chemotherapy regimen, only the dose of Oxaliplatin will be adjusted. That is: when the tumor diameter > 10 cm and there is abundant blood supply, the dose of Oxaliplatin selected is 130 mg/m^2^. For tumors ≤ 10 cm and with less abundant blood supply, the dose of Oxaliplatin selected is 85 mg/m^2^. Additionally, when a large tumor significantly shrinks after several courses of HAIC treatment, a dose reduction may be appropriate, even down to 60 mg/m^2^. Subsequent researchers can make appropriate dose adjustments based on the patient's actual treatment situation and tolerance, and ensure proper documentation.  ***Note**: If a subject permanently discontinues one of the investigational drugs (Donafenib or Sintilimab) due to adverse reactions, and the investigator assesses that the subject may still benefit from continuing the other drug in combination with HAIC treatment, the subject may receive treatment with the other drug in combination with HAIC in this study. If a subject permanently discontinues both drugs due to adverse reactions, the subject must permanently withdraw from the study treatment. |

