## Dose selection basis

### 3.3.1 Donafenib tablets

In this study, the dose of donafenib is 200mg Bid. 200mg Bid is the standard dosing regimen for donafenib in phase III clinical trials for first-line treatment of advanced hepatocellular carcinoma. An exploratory study of 6 patients with advanced gastrointestinal tumors (including 4 cases of liver cancer) treated with 100 mg Bid of donafenib combined with 240 mg Q2W of Sintilimab showed that the overall safety profile of the combination therapy was similar to that of either Sintilimab or donafenib monotherapy, with no unexpected adverse reactions occurring (data not yet published).

This study includes a safety lead-in phase, where the first 6 subjects enrolled in the study will undergo gradual safety monitoring. Each patient will receive oral administration of donafenib tablets [200 mg, Bid] combined with intravenous infusion of Sintilimab injection [200 mg, Q3W], and will receive HAIC treatment on the same day or the following day after Sintilimab infusion. The monitoring window is from the first administration of donafenib treatment to 21±3 days after the first HAIC treatment (i.e., from D1 of the donafenib monotherapy period to C2D1 of the combination therapy period). If ≥2 cases of dose-limiting toxicity (DLT) are observed among the first 6 subjects, and the research team assesses that the toxicity is solely related to donafenib treatment, the initial dose for subsequent enrolled patients receiving donafenib treatment will be adjusted to 100 mg Bid.

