## 3.4 DLT Assessment and Judgment Criteria

DLT is defined as any of the following adverse events, unless the investigator determines that it is definitely related to the study progression or caused by other external factors, it will be considered as DLT:

Hematologic Toxicity:

- - - 1. Grade 4 neutropenia lasting more than 7 days.
      2. Febrile neutropenia [defined as an absolute neutrophil count (ANC) < 1×10^9^ /L, accompanied by a single temperature reaching 38.3℃ or a temperature of 38℃ persisting for more than one hour].
      3. Grade 3 neutropenia with infection.
      4. Grade 3 thrombocytopenia with severe uncontrollable bleeding events.
      5. Grade 4 thrombocytopenia.
      6. Grade 4 anemia (life-threatening).
      7. Grade 3 or 4 lymphopenia with opportunistic infections.

Non-hematologic toxicity:

Skin reactions: severe hand-foot skin reaction (HFSR) or other skin adverse reactions that persist for >2 weeks or occur a second time despite appropriate intervention.

Blood pressure: persistent/recurrent systolic blood pressure ≥160 mmHg or diastolic pressure ≥100 mmHg on the second occurrence, and remains uncontrolled despite aggressive antihypertensive treatment. (Persistent/recurrent blood pressure ≥160/100 mmHg refers to measurements of ≥160/100 mmHg taken at least twice with an interval of 24 hours, with each measurement taken after the subject has been seated and resting quietly for more than 5 minutes.) At least 1 week of antihypertensive medication is allowed before the second recorded hypertension event occurs.

Cardiac contractile function: First occurrence of LVEF decrease >10%, or LVEF value <40%.

Gastrointestinal system: Grade 4 diarrhea, or Grade 3 diarrhea lasting >24 hours despite active antidiarrheal treatment, or occurrence of two episodes of Grade 3 diarrhea regardless of duration; Occurrence of ≥ grade 3 nausea and vomiting despite adequate/maximum medical intervention and/or preventive measures.

Absolute QTcB ≥500 msec (at two consecutive time points).

Other Grade 4 or higher adverse events.

Grade 3 or higher immune-related adverse events (irAE).

Other Grade 3 toxic effects, except for laboratory abnormalities that recover to Grade 2 (inclusive) or below within 3 days (asymptomatic and not requiring medical intervention).

In addition to the above events, DLT events also include any level of toxic reaction that the investigator considers necessitating the subject's withdrawal from the study.

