## Criteria for Termination of Study

### Early Termination of the Study

The investigator may terminate this study at any time, with reasons for early termination including but not limited to:

1. The discovery of unexpected, significant, or unacceptable risks to subjects enrolled in the study during the study period;
2. The discovery of significant errors in the clinical research protocol during the study period, making it difficult to evaluate the investigational drug;
3. Request for termination by health/regulatory authorities.

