## Dose adjustment/suspension of medication

**donafenib tablets:**

1) The initial dose adjustment scheme is 200 mg bid

During the treatment period, if the subject experiences grade 4 hematologic toxicity or grade 3 non-hematologic toxicity related to the investigational drug, the medication will be temporarily suspended (according to NCI CTCAE V5.0 standards), only allowing the subject to undergo a maximum of 2 dose adjustments. If grade 4 hematologic toxicity or grade 3 non-hematologic toxicity cannot return to normal or CTCAE grade 1 within 2 weeks after suspension, the medication will be permanently discontinued. (Grade 3 or higher adverse reactions do not include alopecia, uncontrolled nausea/vomiting, uncontrolled allergic reactions, and asymptomatic laboratory test abnormalities)

After the first suspension of medication, if the adverse reactions recover to ≤ Grade 1 within 1 week, continue taking the original dose; If recovery to ≤ Grade 1 occurs within 2 weeks of drug suspension, the dose is reduced to 200 mg qd to continue treatment; After dose adjustment, if drug suspension occurs again, and recovery to ≤ Grade 1 occurs within 2 weeks, the dose is reduced to 200 mg qod to continue treatment. If grade 4 hematologic toxicity or grade 3 non-hematologic toxicity occurs again (the 3rd occurrence), the drug will be permanently discontinued. That is Dose adjustment plan:

| Initial dose | First dose reduction | Second dose reduction |
| --- | --- | --- |
| 200 mg bid | 200 mg qd | 200 mg qod |

2) Dose adjustment scheme when the initial dose is adjusted to 100 mg bid due to DLT

If ≥2 cases of dose-limiting toxicity (DLT) are observed among the first 6 subjects, and the research team assesses that the toxicity is solely related to donafenib treatment, then the initial dose adjustment for subsequent enrolled patients receiving donafenib treatment will be 100 mg bid. At this time, the dose adjustment follows the same principles and processes as normal dose adjustments, with specific dose changes as follows:

| Initial dose | First dose reduction | Second dose reduction |
| --- | --- | --- |
| 100mg bid | 100mg qd | 100mg qod |

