**Sintilimab injection:**

Throughout the study, dose adjustments for sintilimab are not permitted; the principles for pausing and permanently discontinuing sintilimab administration are outlined in Table 1.

If a subject experiences a grade 2 drug-related irAE or a grade 3 or higher other AE (refer to the ESMO guidelines for the management of toxicity related to immune checkpoint inhibitors), the subject must suspend administration, with a maximum delay of 7 days; subsequent administration schedules will be adjusted accordingly. If the administration is delayed for more than 7 days, it will be considered a missed dose, and the subject will receive the next cycle of administration according to the original schedule (calculated from the date of the first administration). If treatment-related adverse reactions have not recovered to grade 0-1 or baseline levels within 6 weeks after the last dose of Sintilimab, then Sintilimab should be permanently discontinued. If a subject discontinues the medication for more than 6 weeks and the investigator determines that the risks of continuing administration outweigh the benefits, they may permanently withdraw from the study treatment.

If a subject requires a gradual reduction in dosage of steroids due to an adverse event, the recombinant humanized anti-PD-1 monoclonal antibody may be discontinued for a longer period until the steroid tapering is completed or reduced to a prednisone dose of ≤10 mg/day (or equivalent dose). If the discontinuation exceeds 6 weeks (with the maximum discontinuation time for sintilimab due to steroid tapering not exceeding 12 weeks), the investigator may reassess the overall risk-benefit evaluation before resuming the use of the recombinant humanized anti-PD-1 monoclonal antibody.

Subjects may interrupt administration for reasons other than toxic reactions (such as surgical procedures), with the interruption not exceeding 6 weeks. The investigator may restart the use of recombinant humanized anti-PD-1 monoclonal antibody *based on an overall risk-benefit assessment.*

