### Immune-related adverse events (irAE)

Recombinant humanized anti-PD-1 monoclonal antibody may be associated with the following significant irAEs: immune-related liver dysfunction, interstitial lung disease, pancreatitis, endocrine disorders [hypothyroidism (for replacement therapy of hypothyroidism, see [Appendix 8](#附录十) ), hyperthyroidism], and immune-related hyperglycemia.

In addition, irAEs also include the following clinically significant potential events: exfoliative dermatitis, pigmentary retinopathy, arthritis, myocarditis, hemolytic anemia, partial seizures that may occur in subjects with inflammation in the cerebral hemispheres, adrenal insufficiency, myasthenia gravis, optic neuritis, and rhabdomyolysis.

For suspected irAEs, close monitoring of the relevant system functions is required, and a thorough evaluation should be conducted to determine the cause and exclude other reasons. Overall, based on the severity of the events, it may be necessary to suspend or permanently discontinue the recombinant humanized anti-PD-1 monoclonal antibody and/or provide symptomatic treatment, such as corticosteroids. When administering 1-2 mg/kg of prednisone or a glucocorticoid with equivalent efficacy, a gradual dose reduction should begin after the event has been alleviated to grade 0-1. If the irAE remains at grade 0-1 at this time, re-administration of recombinant humanized anti-PD-1 monoclonal antibody therapy should be considered. In the event of an irAE of grade 3 or higher (excluding endocrine system diseases), immediate permanent discontinuation of the drug and withdrawal from the study is required.

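### The six-patient lead-in counts DLTs from all three components but acts only on toxicity due solely to donafenib, so other DLTs have no stated consequence for subjects 7 to 30

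*Protocol*

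**What the plan says.** The first six subjects receive donafenib 200 mg bid, sintilimab 200 mg every three weeks and HAIC. They are watched for DLTs from the first donafenib dose until 21±3 days after the first HAIC (Protocol Summary, Administration dose; Section 3.3.1).

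The DLT list in Section 3.4 is not tied to one component. It leaves out only events put down to progression or to external factors. It covers haematological toxicity, most other grade 3 and all other grade 4 events, and "Grade 3 or higher immune-related adverse events (irAE").

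One cohort-level consequence is attached. It needs two or more DLTs in the first six and one further condition: "and the research team assesses that the toxicity is solely related to donafenib treatment". What follows when both are met concerns donafenib alone, as Section 5.3 puts it: "the initial dose adjustment for subsequent enrolled patients receiving donafenib treatment will be 100 mg bid". The same condition stands in the Protocol Summary, Section 3.3.1 and the donafenib part of Section 5.3. The dose adjustment scheme in the Protocol Summary refers back to this step as a reduction "due to the observation of ≥2 cases of DLT in the first 6 patients", without the attribution condition.

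For sintilimab, "Throughout the study, dose adjustments for sintilimab are not permitted"; it can only be held or stopped in the individual subject. HAIC dosing is individualised. After a non-endocrine immune-related event of grade 3 or higher, "immediate permanent discontinuation of the drug and withdrawal from the study is required" (Section 8.4.3). Section 4.3.1 lets the investigator end the study on grounds that include "The discovery of unexpected, significant, or unacceptable risks to subjects enrolled in the study during the study period".

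**The concern.** A lead-in exists to decide what later subjects should start on. Here the count covers the whole triplet, but a decision is attached to one cause only. The rule calls for a causal judgement, then says what follows from one possible answer and nothing about the others: sintilimab, HAIC, several components together, or cause undetermined.

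Those other answers are not remote. Donafenib is given alone for only 3 to 7 days, and for the rest of the window all three components are on board. For a cytopenia, a transaminase rise or diarrhoea, sole attribution to donafenib will be hard to establish. The causality criteria in Section 8.5 grade relatedness but define no category for a sole cause.

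The stakes are safety. The donafenib-sintilimab experience cited in Section 3.3.1 is six patients "treated with 100 mg Bid of donafenib combined with 240 mg Q2W of Sintilimab", half the donafenib dose used here and with no HAIC mentioned. The two HAIC triplet series in Section 1.5 used lenvatinib and toripalimab. The protocol cites no data on this triplet, so the lead-in is the first check on it.

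**Working it through.** The protocol gives no target DLT rate or operating characteristic for the lead-in, so there is no stated figure to reproduce. The logical check comes first, then its size.

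**Outcomes with two or more DLTs in six**

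| Judged cause | Stated consequence for later subjects |
|---|---|
| Solely donafenib | Donafenib 100 mg bid (Summary, 3.3.1, 5.3) |
| Sintilimab | None; holds and discontinuations act on the individual subject (5.3, 8.4.3) |
| HAIC | None; oxaliplatin dose is adjusted per subject (5.3) |
| Overlapping or undetermined | None |

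Discretionary termination under Section 4.3.1 is open in every row, but it has no threshold and no link to the DLT count.

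**Inputs**
- From the protocol: n = 6 lead-in subjects; trigger at 2 or more; 30 subjects in total, so 30 − 6 = 24 follow the lead-in (before any lead-in replacements).
- Assumed: p, the probability that a subject has a DLT (10%, 30%, 50%); f = 0.5, the share of DLTs solely due to donafenib; independent subjects, with DLT cases counted as subjects.

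**Formulas**
- Any cause: P(X ≥ 2) = 1 − (1−p)^6 − 6p(1−p)^5. At p = 0.3: 1 − 0.1176 − 0.3025 = 0.580.
- Reading A, at least two DLTs solely due to donafenib: the same formula with p·f in place of p. At p = 0.3, p·f = 0.15: 1 − 0.3771 − 0.3993 = 0.224.
- Reading B, two or more DLTs and every one solely due to donafenib: (1−p+pf)^6 − (1−p)^6 − 6pf(1−p)^5. At p = 0.3: 0.3771 − 0.1176 − 0.1513 = 0.108.
- Two or more DLTs with no stated action: any cause minus A, or any cause minus B.

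| p | Any cause | Action, A | Action, B | No action, A | No action, B |
|---|---|---|---|---|---|
| 0.10 | 0.114 | 0.033 | 0.027 | 0.082 | 0.088 |
| 0.30 | 0.580 | 0.224 | 0.108 | 0.356 | 0.472 |
| 0.50 | 0.891 | 0.466 | 0.115 | 0.425 | 0.775 |

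The result depends heavily on f. If no DLT is solely due to donafenib (f = 0), the action never triggers at any DLT rate. If all are (f = 1), it triggers whenever the count reaches two and the gap closes. At p = 0.50 the rule therefore acts with probability anywhere from 0 to 0.891, depending on attribution alone.

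Section 1.5 reports grade 3-4 treatment-related event rates of 72.2% and 28.0% in the two lenvatinib-based series. These are not DLT rates for a short window and were not used as inputs.

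**The case against.** The strongest reply is that the rule is a donafenib dose-selection rule and is coherent as one. It sits under the donafenib headings, and donafenib is the only component with an alternative starting dose. Sintilimab follows its label and HAIC the centre's routine. That explains why the dose *step* is donafenib-only. It does not say what happens to enrolment when the count is reached for another cause.

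Other safeguards exist:
- Every subject must tolerate donafenib alone before the combination starts.
- Patient-level holds and withdrawals apply to each drug.
- Serious adverse events go to the regulator and ethics committee within 24 hours (Section 8.7.2).
- Section 1.6 promises a risk management plan, which is not at hand.
- The investigator may end the study at any time, on grounds that are not limited to those listed.

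These lower the risk in practice, but none gives a defined consequence for two non-donafenib DLTs in six.

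Three points against the detail have force. The shorter wording in the Summary's dose adjustment scheme is most likely shorthand, so it is a matter of tidying and not a second rule. The probabilities rest on assumed inputs. And Reading B is the less natural one: an extra non-donafenib DLT would cancel a reduction that two donafenib DLTs had already earned. It alone supplies the upper figures of 47% and 78%.

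**Conclusion.** The concern holds and should be fixed. Followed as written, two or more DLTs from sintilimab, HAIC or overlapping toxicity leave the 24 later subjects on an unchanged starting regimen with no required review. Confidence in this reading is high, because it follows from setting the DLT list beside the action clause.

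The size is illustrative only. With half of DLTs solely due to donafenib, and on the more natural reading that at least two must be so attributed, the uncovered outcome has a probability of about 8%, 36% and 42% at DLT rates of 10%, 30% and 50%. The protocol supplies neither the DLT rate nor the attribution share. A secondary ambiguity also stands: the text does not say whether all DLTs, or only two, must be solely due to donafenib.

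**What to change.** In the Protocol Summary (Administration dose), Section 3.3.1 and Section 5.3, add: *As soon as two of the first six subjects have had a DLT, whatever its attribution, enrolment of new subjects pauses for a documented safety review that decides whether to continue, modify or stop.*

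Keep the 100 mg bid step for donafenib-attributed toxicity, state whether all or at least two DLTs must be so attributed, and align the wording in the Summary's dose adjustment scheme.

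The outcome of the review stays a matter of judgement, but the review becomes mandatory at a fixed threshold, which Section 4.3.1 does not provide. No hold applies while fewer than two subjects have a DLT, so some later subjects could start before the second DLT is recorded.

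The cost is one sentence in three places and one alignment, with no added visits or tests. The downside is a possible short enrolment pause, with probability 11%, 58% or 89% at assumed DLT rates of 10%, 30% or 50%.

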## Safety Analysis

A descriptive summary table will be provided for all safety parameters. Summarize adverse events and adverse reactions (defined as 'definitely related, possibly related, or indeterminate relationship to the investigational drug' AEs) that occurred during treatment according to CTCAE V5.0 grading, calculate the incidence of AEs, list the frequency and count of AEs by system, and calculate percentages, along with a detailed list of various AE cases. Analyze the occurrence of AEs, and evaluate the safety of the investigational drug in conjunction with vital signs and laboratory test results during the treatment process.

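### Section 5.3 exempts asymptomatic laboratory abnormalities from the donafenib toxicity rule and the Protocol Summary does not, so the same patient can be permanently stopped under one text and not the other

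*Protocol*

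**What the plan says.** The donafenib rule is written out twice.

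- **Protocol Summary, Dose adjustment scheme.** The trigger is "If grade 4 hematologic toxicity or grade 3 non-hematologic toxicity occurs, temporarily discontinue the drug". The permanent stop reads "If recovery to normal or CTCAE Grade 1 cannot be achieved within 2 weeks after stopping the medication, then permanently discontinue the medication". The Summary also gives the one-week and two-week recovery steps, the reduction tables, the limit of two adjustments and the stop at a third occurrence. It contains no exemptions.
- **Section 5.3, donafenib tablets.** The drug is suspended when a subject "experiences grade 4 hematologic toxicity or grade 3 non-hematologic toxicity related to the investigational drug". The stop applies when such toxicity "cannot return to normal or CTCAE grade 1 within 2 weeks after suspension, the medication will be permanently discontinued". Directly after that sentence comes a parenthesis: "Grade 3 or higher adverse reactions do not include alopecia, uncontrolled nausea/vomiting, uncontrolled allergic reactions, and asymptomatic laboratory test abnormalities".

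Nothing says which text governs.

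The documents also differ on what follows a long interruption. If one drug is permanently discontinued for adverse reactions and further benefit is judged possible, the Summary note says "the subject may receive treatment with the other drug in combination with HAIC in this study". Section 4.3.2 item 3 and the note closing section 5.3 say the same in substance. Section 5.4.5, donafenib item 4, says instead that a subject whose donafenib is interrupted on the investigator's recommendation for more than two weeks has to leave the study.

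**The concern.** These are mandatory patient-level safety instructions, and the two versions do not cover the same events. The Summary is not shorthand that sends the reader elsewhere for exceptions. It is complete enough to act on, and a reader of it has no sign that an exemption exists.

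At stake is whether a patient with an abnormal but silent liver test keeps donafenib, loses it for good or, through 5.4.5, leaves the study. Elevated AST and thrombocytopenia are foreseeable here: section 1.5 reports each at 13.9% among grade 3-4 treatment-related events with a comparable triplet.

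The exemption in 5.3 cannot simply be copied into the Summary to cure this, because as printed it undercuts 5.3's own trigger.

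**Working it through.** The plan gives no figure to reproduce, so the check applies each text to specific cases. The parenthesis in 5.3 follows the permanent-stop sentence, not the hold sentence, so it has two possible readings: *wide* (it lifts the hold and the stop) and *narrow* (it lifts the stop only).

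| Drug-related case | Summary | 5.3, wide | 5.3, narrow |
|---|---|---|---|
| Asymptomatic grade 3 ALT, at grade 1 on day 10 | Hold, then 200 mg qd | No hold | Hold, then 200 mg qd |
| Asymptomatic grade 3 ALT, not at grade 1 by two weeks | Hold, then permanent stop | No hold, no stop | Hold, no permanent stop |
| Asymptomatic grade 4 platelets, not at grade 1 by two weeks | Hold, then permanent stop | Excused from both | Hold, excused from stop |
| Grade 3 vomiting described as uncontrolled, not at grade 1 by two weeks | Hold, then permanent stop | Excused from both | Hold, excused from stop |

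**Row 1** differs only on the wide reading, so a conflict over the hold alone is possible but not certain.

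**Row 2** differs on both readings and is the firm result. On the narrow reading 5.3 also leaves a gap: the patient is held beyond two weeks, is neither stopped nor told how to resume, and then meets the withdrawal rule of 5.4.5 item 4.

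**Row 3** is a contradiction inside 5.3. The exemption speaks of grade 3 or higher and is not confined to non-hematologic values. Both the hold sentence and the stop sentence of 5.3 name grade 4 hematologic toxicity, so the parenthesis collides with at least one of them on either reading. Section 3.4 counts grade 4 thrombocytopenia as a DLT without any symptom condition. A silent grade 4 platelet count in one of the first six subjects could therefore be a DLT and yet be excused by 5.3.

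**Row 4** looks like an inversion. An exemption would normally cover nausea and vomiting that treatment controls. Section 3.4 treats grade 3 or higher nausea and vomiting despite maximum treatment as a DLT. The item on allergic reactions has the same form.

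**Third occurrence.** Both texts stop the drug at the third qualifying toxicity, but they may not count the same events, so the total can differ.

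**Withdrawal.** Take a patient permanently off donafenib because an adverse reaction did not recover in two weeks. The Summary note, section 4.3.2 item 3 and the closing note of 5.3 permit sintilimab plus HAIC. Section 5.4.5 item 4 requires the patient to leave the study. Both cannot be followed.

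**The case against.** The strongest reply is that the two passages largely agree. That is right for the stop rules: two weeks to reach grade 1, third occurrence and two adjustments match in wording. They diverge only through the events that qualify. Several stronger readings are tempting and are not supported:

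- **That 5.3 plainly exempts a silent grade 3 ALT from the hold.** The position of the parenthesis allows the narrow reading.
- **That the texts clash over relatedness.** Only 5.3 states it in the trigger. The Summary's first recovery step, however, reads "if the adverse reactions recover to ≤ Grade 1 within 1 week", and section 10.4 has adverse reactions "defined as 'definitely related, possibly related, or indeterminate relationship to the investigational drug' AEs". Relatedness is therefore largely implied in the Summary.
- **That grade 4 non-hematologic toxicity is left uncovered.** A threshold of grade 3 naturally includes grade 4.
- **That patients who entered with raised liver tests would be forced off donafenib on returning to baseline.** Grading is by CTCAE v5.0, which is linked and not reproduced, and sections 8.7.1 and 8.8.9 support treating a return to baseline as recovery.
- **That adverse-event counts must change.** Section 8.8.5 makes a laboratory value reportable if it alters treatment, but also if it needs medical intervention or is judged clinically significant. The net effect is unknown.

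Safeguards also exist. Section 4.3.2 items 4 and 12 let the investigator end treatment, and laboratory results are reviewed before each cycle from C2D1. They limit the harm but do not say which mandatory rule applies. The comparison with DLT criteria is partial, since DLTs are assessed only in the first six subjects and serve another purpose. The odd *uncontrolled* items are probably a translation slip, but they are the text that staff would follow.

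**Conclusion.** The point holds, with moderate confidence, and should be fixed. Three things are established:

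- An asymptomatic, drug-related grade 3 non-hematologic laboratory value that is not back to grade 1 within two weeks leads to a permanent stop under the Summary and not under 5.3, whichever way the parenthesis is read.
- The exemption, read literally, excuses asymptomatic grade 4 hematologic values that 5.3 itself names.
- The withdrawal requirement in 5.4.5 item 4 contradicts three other places.

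Whether the hold also differs depends on an ambiguity only the protocol authors can settle.

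The size in patients cannot be given. The 13.9% figures come from a regimen with a different kinase inhibitor and a different PD-1 antibody. They are not split by symptoms or by recovery within two weeks. A reader might infer a bias in the response rate, but nothing in the protocol allows one to be estimated.

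**What to change.** - Put one trigger in both the Summary and 5.3: drug-related grade 4 hematologic or grade 3 or higher non-hematologic toxicity.
- State whether the laboratory exemption applies to the hold, the stop or both, and limit it to asymptomatic grade 3 non-hematologic values. Dropping it and keeping the Summary's stricter rule would equally remove the conflict; that choice is clinical.
- Correct the items on uncontrolled nausea/vomiting and uncontrolled allergic reactions after checking the source-language text.
- Make section 5.4.5 item 4 agree with the Summary note, section 4.3.2 item 3 and the closing note of 5.3, for example by ending donafenib while allowing sintilimab plus HAIC where benefit is expected.

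The cost is a wording amendment to two dose-adjustment passages and one compliance item, with no added visits or tests. The downside of keeping the limited exemption is that some asymptomatic grade 3 laboratory values would no longer lead to the hold or stop that the Summary now requires.
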